MDA is an abused drug with poorly documented effects. The risks of modest single oral doses of MDA to healthy experienced volunteers is low, while the potential benefits to society of improved understanding of MDA pharmacology are high.

4.	METHODS: 

This is a double-blind, placebo-controlled clinical study occurring in a hospital setting.  The study uses a Latin-square balanced design.  Physiological, pharmacokinetic, hormonal, genetic, subject-rated, observer-rated, and behavioral measures are made at timed intervals before and after study drug administration.

(4a) General Study Design:  

The study uses a double-blind, placebo-controlled, Latin-square design.  Volunteers will be 12 healthy people not DSM-IV dependent on any substance (other than nicotine or caffeine).  All must have self-report experience with either MDA alone or have used separately both MDMA and a hallucinogen, such as LSD or psilocybin.  After careful screening at our laboratory, subjects will be admitted to the Clinical and Translational Science Institute Clinical Research Center (CCRC) at San Francisco General Hospital (SFGH). for 4 days and 3 nights.  Subjects are admitted to the CCRC the day before the first experimental session.  Experimental session 2 occurs 24 hours after the first dosing session, and final measures are collected on the 4th day. Subjects will be discharged on the 4th day in the late afternoon or early evening.  On the experimental dosing days subjects are dosed at approximately 10am and measures/data are collected at set time points throughout the inpatient stay.  Screening and the End of Study Visit take place in our laboratory and the inpatient portion of the study occurs at the CCRC at San Francisco General Hospital (SFGH).  Dosing takes place at approximately 10 am each day.  Sessions begin 24 hours apart on consecutive days and each session follows the exact same time course.  Subjects will come for follow up at APRL on one occasion between 1-4 weeks after discharge for additional safety monitoring. Briefly, the time schedule for the study is shown in Table 1, below.

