Screenings visits will take place at the CPMC Addiction Pharmacology Research Laboratory at St. Luke's Hospital (APRL) and will be 1 - 5 hours duration each (approximately 6 hours in total).  Subjects will be inpatient for approximately 70 consecutive hours and the final End-of-Study follow up visit at APRL will take approximately 1 hour.  In total, subject participation will last about 77 hours.  

Subjects will not be paid for any of the screening visits.  For each day or part of a day spent at the CCRC subjects are reimbursed $100.  Subjects will be paid $25 for the follow up visit and will also receive a 20% bonus if they have completed the entire study, making total reimbursement $510.

Purpose:	 	Screening

	Approx. 5 days until CCRC admission	DAY 1
Drug or Placebo Session 1

INPATIENT	DAY 2
Drug or Placebo Session 2

INPATIENT	
DAY 3
Post-dose measures/data collection & Discharge

	                    Approx. 2 weeks	
End-of-Study

Follow-up	
Time:	 	6 hrs over 2-4 visits		10 hrs active
Measures collected 10am-8pm 
	10 hrs active
Measures collected 10am-8pm 
	7 hrs active
Measures collected 9am-4pm
		
1 hr.	
		

	(4b) Procedures: 

Screening Visits: 

Subjects will initially contact the laboratory by telephone.  Following successful initial phone contact, potentially eligible subjects will visit the laboratory.

Depending on the scheduling requirements of the individual, the following 6-hr screening process will take place over 2 to 4 visits:
 
First, the consent is given to the subject to read, reviewed with the subject. Following this subjects will answer the consent questionnaire and will then sign the informed consent. Demographic and screening information will then be obtained. Subjects will then give a sample for urine analysis and females will provide urine for a pregnancy test. The pregnancy test has to be negative for females to participate in the study.   Presence or absence of dependence will be initially determined during the phone screen and confirmed during the on site screening process and physical. 

Questionnaires for estimating use patterns of MDMA, MDA, and other drugs will be administered (i.e., MDMA route of administration and lifetime use questionnaires).  The NEO-FFI is administered to record personality.  A 12-lead EKG, blood and urine samples will be taken.  A brief neurocognitive testing battery is performed. 

Blood testing will include: 
·	Complete blood count
·	Comprehensive blood chemistry panel 

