Source and Storage of study drugs:  Under supervision of the Food and Drug Administration, we will synthesize MDA in our laboratory.  We will assess identity, stability, and purity to their satisfaction.  MDA will be stored and handled according to federal, state, and local regulations. MDA will be stored in our safe using procedures approved by the DEA.

Study Measures are similar or identical to those used in our past and ongoing studies to facilitate comparisons between MDA and related compounds.  Below we list timing of measures followed by measure descriptions.
Timing of Measures:
Plasma for MDA & Metabolites: Pre and 1, 2, 4, 6, 8, 12, 26, and 30 hrs after MDA or Placebo.
Urine for MDA & Metabolites: Urine samples at 0-8 and 24-48 hrs after MDA or Placebo dosing..
Plasma or serum (as appropriate) for oxytocin (which will be frozen and sent to [name]): Predose and 1, 2, 3, and 4 hours after dosing.  
Plasma or serum (as appropriate) for cortisol and prolactin: Predose, 2, and 3 hours after dosing.  

Heart rate, blood pressure, impedance cardiography, skin and core temperatures, visual analogue scales: Predose and 0.5, 1, 1.5, 2, 2.5, 3, 4, 6, 8, 24, and 30 hours after dosing 
BSI: Predose and 24 hours after MDA or Placebo (to measure possible residual drug effects).
Subjective drug effects questionnaire (SDEQ): At 7 hours after dosing and before discharge on Day 3. 
APZ-OAV and Hood M-Scale:  At 7.5 hours after dosing and before discharge on Day 3.
AVI and IAS-R: Predose, 2.5, 7.5 and 29 hrs after dosing and before discharge on Day 3.
Brief Fear of Negative Evaluation (BFNE) and State-Trait Anxiety Instrument – State (STAI):  Predose and once during peak drug effects (1 – 2.5 hours postdose).
Emotional Face Task and Famous Face task: During peak drug effects (1 – 2.5 hours postdose).
Dot Probe Task:  at 2hr. post dose.
Neurocognitive battery (Visual Functioning Battery):  3 hours after MDA or Placebo (to measure possible residual drug effects).
EEG:  3 hrs after MDA.
Written description of drug effects:  10 hours after dosing.

Descriptions of Measures
Pharmacokinetic and Hormonal Measures
Blood is sampled through an indwelling intravenous catheter placed by licensed medical personnel.  Each sample requires 7 ml or less, making the total required in each of the two experimental sessions 146 ml.
All urine is collected, with the pH determined before acidification and storage with timed samples reflecting predose and the 0-8 and 8-30 hrs after MDA.

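### Two conflicting urine schedules: 0-8/24-48 h leaves a gap and is cut short when MDA is given second, and 0-8/8-30 h overlaps the next session unless split at the second dose

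*Protocol*

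**What the plan says.** Section 4b of the protocol describes urine collection twice.

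- Timing of Measures, in the line for MDA and metabolites: "Urine samples at 0-8 and 24-48 hrs after MDA or Placebo dosing".
- Descriptions of Measures, under Pharmacokinetic and Hormonal Measures: "All urine is collected, with the pH determined before acidification and storage", with "timed samples reflecting predose and the 0-8 and 8-30 hrs after MDA".

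The timeline that these windows must fit is in section 4a. "Experimental session 2 occurs 24 hours after the first dosing session" and "Dosing takes place at approximately 10 am each day". In the schedule table, the day after session 2 reads "Measures collected 9am-4pm". The text adds "Subjects will be discharged on the 4th day in the late afternoon or early evening" and "Subjects will be inpatient for approximately 70 consecutive hours". No outpatient urine collection is described. Section 4a also says that both sessions follow the same time course, and the study is double-blind.

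Aim 1 is the pharmacokinetics of MDA, and hypothesis 1 is its metabolism to HMA and DHA. Section 4c names a compartmental model of concentration against time as the pharmacokinetic analysis.

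**The concern.** Staff cannot follow both schedules, and urine that has been pooled and acidified cannot be separated later. The choice between them has to be made before the first volunteer is admitted.

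The timing list leaves the hours from 8 to 24 unassigned, and its 24-48 h window runs past the inpatient stay for anyone who receives MDA in session 2. The measure description is contiguous, but its 8-30 h window after session 1 crosses the second dose at hour 24. At stake is whether the amounts of MDA and its metabolites in urine can be summed over the same period in both sequences. With 12 volunteers and balanced dose order, a fault confined to one sequence affects about half the sample.

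**Working it through.** **1. The protocol's timeline.** Set t = 0 at the session-1 dose, about 10 am.
- The session-2 dose is at t = 24 h.
- The last inpatient measures, at 4 pm the day after session 2, are at t = 24 + 30 = 54 h.
- A 70 h stay ending at t = 54 begins at 54 - 70 = -16 h, which is 6 pm the evening before. This agrees with admission on the day before session 1.
- The stated total participation also reproduces: 6 + 70 + 1 = 77 h.

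**2. The windows on that timeline, counted from the MDA dose.**

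| Window | MDA in session 1 | MDA in session 2 |
|---|---|---|
| 0-8 h | t = 0 to 8, collectable | t = 24 to 32, collectable |
| 24-48 h | t = 24 to 48, collectable | t = 48 to 72, but measures end at 54: 18 of 24 h lost |
| 8-30 h | t = 8 to 30, collectable, crosses a placebo dose | t = 32 to 54, collectable |

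The 0-8/24-48 h version omits 24 - 8 = 16 of the first 48 hours. Its wording covers placebo as well as MDA. In placebo-first volunteers, 24-48 h after placebo is therefore t = 24 to 48, which is 0-24 h after MDA and overlaps session 2's own 0-8 h pool.

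**3. Size of the gap, under an assumption.** The protocol gives no half-life and says that MDA pharmacokinetics have not been characterized. Assume first-order loss of parent drug, no absorption delay and a half-life h of 6 to 12 hours. The share excreted between a and b hours is then exp(-ka) - exp(-kb), with k = ln 2 / h.

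| Half-life | 8-24 h (omitted) | 0-8 plus 24-48 h (MDA first) | 0-8 plus 24-30 h (MDA second) | 0-30 h continuous |
|---|---|---|---|---|
| 6 h | 0.334 | 0.662 | 0.634 | 0.969 |
| 8 h | 0.375 | 0.609 | 0.551 | 0.926 |
| 10 h | 0.385 | 0.579 | 0.490 | 0.875 |
| 12 h | 0.380 | 0.558 | 0.443 | 0.823 |

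For example, at 12 h with MDA second: (1 - 0.630) + (0.250 - 0.177) = 0.443.

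The MDA-second column counts only windows timed from the MDA dose. If hours 8-24 after MDA were kept in a pool labelled as placebo 24-48 h, that urine would exist under the wrong label. Coverage would still differ between sequences.

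**4. The overlap under 0-8/8-30 h.** If blinded staff apply the same pools to both sessions, t = 24 to 30 belongs both to session 1's 8-30 h pool and to session 2's 0-8 h pool. Suppose the session-1 pool takes those six hours in a placebo-first volunteer. The MDA 0-8 h sample then contains only hours 6-8. The share of its content lost is (1 - exp(-6k)) / (1 - exp(-8k)):
- half-life 6 h: 0.500 / 0.603 = 0.83
- half-life 12 h: 0.293 / 0.370 = 0.79

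If session 2 takes those hours instead, the session-1 pool ends at 24 h rather than 30 h.

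**The case against.** The measure description is tied to MDA, not to MDA or placebo. Read literally, it is contiguous, can be collected to exactly 30 h in both sequences and has equal length in each. In MDA-first volunteers it crosses only a lactose capsule, so no MDA is added. Because all urine is to be collected, the 8-24 h gap appears only if the timing list is followed and that sentence is set aside. A void near the second dose is also suggested by the predose sample and the urine toxicology screen before each session.

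All of this stands, and it narrows the problem under the 0-8/8-30 h version to placebo-first volunteers. It does not remove it. Staff who do not know which capsule was given cannot apply a window to the MDA session only, and nothing says that the session-1 pool closes at hour 24.

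A reader might go further and infer that urinary recovery of MDA, HMA and DHA would be wrong. The protocol does not support that. It names neither urinary recovery nor renal clearance as an outcome. The stated analysis models concentrations, and hypothesis 1 as worded is qualitative, so plasma or either urine schedule could bear on it. Nor does the single-exponential calculation describe metabolites, whose appearance is delayed by formation.

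**Conclusion.** The two schedules contradict each other and must be reconciled. The contradiction, the 8-24 h gap, the 18 h lost from the 24-48 h window when MDA is second and the 6 h overlap all follow from the protocol's own times.

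Under 0-8/24-48 h, cumulative excretion cannot be computed and coverage depends on sequence. Under 0-8/8-30 h, excretion to 30 h is obtainable in both sequences. The risk there is misallocation in placebo-first volunteers, and it arises only if the same pools are used in both sessions without a split at hour 24.

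The percentages (56-66% against 44-63%, and 79-83% of the 0-8 h sample) are illustrations for parent drug at an assumed half-life of 6-12 h. They should not be read as estimates for HMA or DHA. This is an inconsistency that should be corrected before collection starts; it does not invalidate the planned pharmacokinetic model.

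**What to change.** Replace both lines with one inpatient schedule, the same for every volunteer and without overlap:

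- predose;
- session 1: 0-8 h and 8-24 h, the latter closed by a void just before the session-2 dose;
- session 2: 0-6, 6-8, 8-24 and 24-30 h;
- volume and pH recorded for each pool.

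Delete 24-48 h as a per-session requirement. For MDA-first volunteers, the session-2 0-6 h pool is the 24-30 h interval after MDA. For MDA-second volunteers, the 0-6 and 6-8 h pools add up to 0-8 h. Excretion over 0-24 h and 0-30 h can then be reported on equal terms in both sequences without breaking the blind. The split at 6 h is needed because a plain 24-30 h interval after session 1 would overlap session 2's 0-8 h pool again.

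Cost: no extra collection, since all urine is already to be collected. There are six post-dose pools per volunteer, against four if either existing schedule is applied in both sessions. That is two more to assay each, or 2 x 12 = 24 in all, plus timed voids before the second dose and at hour 6 of session 2.

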Nonetheless, it will be common knowledge that participants in this experiment are required to have past use of MDA or MDMA.  Therefore, in the consent form and in discussions, we caution potential participants that anyone having strong concerns about their past use of drug use being revealed should not participate in this research.  To minimize these risks, we are applying for a Certificate of Confidentiality.  

PROTECTION AGAINST RISK

Volunteer Discontinuation, Dropout or Dismissal.  A volunteer may drop out of the study at any time if he/she so chooses or if the investigator feels it is clinically appropriate.  A volunteer will be dismissed from the study due to a serious or unexpected adverse experience or a serious concurrent illness that warrants withdrawal of the subject from the study.  Subjects who use illicit drugs that could interact with study drugs or who otherwise fail to follow study procedures can be dismissed.  

Subject Safety Monitoring and Test Termination.  Using self-report questionnaires and a general medical exam with a physician, nurse, or nurse practitioner, subjects will be screened to eliminate those with significant medical or psychiatric problems.  Special attention is given to allergies and past adverse reactions to MDA, MDMA, and any other stimulants or hallucinogens. If adverse effects should occur, medical treatment will be immediately available. We have extensive experience in measurements in pharmacology/pharmacodynamic studies. A hospital maintained crash cart, oxygen and emergency ventilation equipment (Ambubags) are immediately available. Physiological monitoring of blood pressure, heart rate, body temperature, and subjective ratings will be carried out before dosing and until acute effects resolve (typically around 6 hrs) to ensure that there are no serious adverse physical or psychological effects of MDA.  Throughout the study, particular attention is paid to the rare MDMA-related acute hyperthermia that might also occur with MDA.  Methods of protecting against this risk are described below. 

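### Readings scheduled at 29 h and 30 h after session 1 fall 5 h and 6 h after the session 2 dose, so as written the late MDA-minus-placebo contrast is biased or cannot be formed within volunteer

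*Protocol*

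**What the plan says.** Section 4b, Timing of Measures, sets the times after dosing. For affect and interpersonal style it lists "AVI and IAS-R: Predose, 2.5, 7.5 and 29 hrs after dosing and before discharge on Day 3". For the cardiovascular and temperature measures and the visual analogue scales (VAS) it lists "Predose and 0.5, 1, 1.5, 2, 2.5, 3, 4, 6, 8, 24, and 30 hours after dosing". Plasma sampling follows the same pattern and names both conditions: "Plasma for MDA & Metabolites: Pre and 1, 2, 4, 6, 8, 12, 26, and 30 hrs after MDA or Placebo".

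Section 4a fixes the spacing of the sessions: "Sessions begin 24 hours apart on consecutive days and each session follows the exact same time course". It adds "Dosing takes place at approximately 10 am each day".

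On how long effects last, the dosing rationale in section 4b expects resolution within 8 hours. The safety monitoring text in section 5b continues monitoring "until acute effects resolve (typically around 6 hrs".

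Section 4c plans a repeated-measures ANOVA on condition and time, with Fisher's LSD comparisons after a significant F test. It sets N at 12 so that dose order can be balanced. No sentence limits the 29 h and 30 h readings to one session, or removes any of them from the analysis.

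**The concern.** A reading taken after the second dose cannot represent the first treatment alone. In a placebo-first volunteer, the values labelled as placebo at 29 h and 30 h are recorded after MDA. In an MDA-first volunteer, the values labelled as MDA at those times are recorded after the placebo capsule. The next treatment's acute effect is thus credited to the previous one. This is the reverse of ordinary carryover, and a carryover adjustment would not remove it.

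The affected measures carry hypotheses 2a (cardiovascular), 2b (AVI positive affect) and 2c (IAS-R affiliativeness). For AVI and IAS-R, 29 h is one of only four hour-indexed readings. A late dip of MDA below placebo could be produced by the schedule and reported as an after-effect of the drug, and the overall condition effect would be understated.

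**Working it through.** **Timing.** Hours after dose 2 = hours after dose 1 - 24, with both doses at about 10:00 (section 4a).

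| Session 1 reading | Clock time, second dosing day | Hours after dose 2 |
|---|---|---|
| 24 h | 10:00 | 0 |
| 26 h (plasma) | 12:00 | 2 |
| 29 h (AVI, IAS-R) | 15:00 | 5 |
| 30 h (cardiovascular, temperatures, VAS, plasma) | 16:00 | 6 |

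The 5 h point lies inside both stated durations of effect. The 6 h point lies inside the 8 h window and at the edge of the 6 h one. Two orders balanced over 12 volunteers give 6 placebo-first, so 6 of 12 placebo profiles (50%) end after MDA.

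**Bias.** Let E be the MDA effect 5-6 h after dosing, and assume no true effect of session 1 treatment remains by 29-30 h. After session 2 no further dose follows, so those late values are clean.
- Placebo-first: MDA minus placebo = 0 - E = -E.
- MDA-first: MDA minus placebo = 0 - 0 = 0.
- Mean over the two orders = (-E + 0)/2 = -E/2.

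The sign and the factor one-half follow from the schedule. Only E is unknown.

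**Size of E.** The protocol gives a planning effect of 28±19 VAS points for MDMA but no effect at 5-6 h. I assume E is 10-75% of 28, that is 2.8 to 21 points. The bias is then -2.8/2 = -1.4 to -21/2 = -10.5 points.

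**SD of the differences.** It is unclear what the protocol's 19 measures. For 28 points, 80% power and two-sided 0.05, a paired t-test needs 6 volunteers if 19 is the SD of the differences. It needs 10 if 19 is the SD within each condition with zero correlation, where the SD of differences is 19 × √2 = 26.9. The stated 11 is nearer the second reading. I therefore use 19 and 27.

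**Chance of a spurious late finding.** Simulation of 12 differences, six of them shifted by -E, with a two-sided paired t-test at 0.05; the entry is the probability of a significant negative result.

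| E (points) | Bias | SD 19 | SD 27 |
|---|---|---|---|
| 0 | 0 | 2.5% | 2.5% |
| 2.8 | -1.4 | 4% | 4% |
| 7 | -3.5 | 8% | 6% |
| 14 | -7.0 | 18% | 11% |
| 21 | -10.5 | 31% | 19% |

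These are for the single late comparison and do not model the preceding F test.

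**Dilution for AVI and IAS-R.** Scale the 2.5 h effect to 1, and let f5 and f7.5 be the effects at 5 h and 7.5 h relative to it. Over predose, 2.5, 7.5 and 29 h:
- Without the overlap: (0 + 1 + f7.5 + 0)/4.
- With it: (0 + 1 + f7.5 - f5/2)/4.
- Relative loss = (f5/2)/(1 + f7.5).

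With f5 = 0.10 and f7.5 = 0.25 the loss is 0.05/1.25 = 4%. With f5 = 0.75 and f7.5 = 0.25 it is 0.375/1.25 = 30%. Setting f7.5 = 0 raises the latter to 38%, but that needs the effect to fall from three quarters of its 2.5 h level to nothing in two and a half hours.

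**The case against.** The strongest reply is that the late readings may belong to Day 3 only. The timetable in section 4a has a Day 3 collection block ending at 4 pm, which is exactly 30 h after a 10 am session 2 dose. The AVI/IAS-R line itself mentions Day 3. Nor does the schedule list a 5 h AVI/IAS-R reading for session 2, so the reading in question would be an extra questionnaire on the second dosing day. This stands as a possible intention, and a reader should not infer that half the placebo profiles will certainly end under MDA. But nothing states it, and it sits badly with the identical timetable for both sessions and with plasma at 26 h and 30 h after either condition. It would not rescue the analysis either. Late MDA values would come only from placebo-first volunteers and late placebo values only from MDA-first volunteers, so no within-volunteer late contrast exists.

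Second, section 4c does not list the time levels that enter the ANOVA, and an analysis plan that is not shown could drop these. That is fair. The point is that the protocol fixes these reading times and a condition-by-time analysis and excludes nothing.

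Third, E may be small. Maximal effects are described at 1.5-3 h for earlier MDA studies and for MDMA, and resolution typically at around 6 h, so E at 30 h could be close to zero. This stands, and is why the range starts at 10%.

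A reader might also infer two stronger things. One is that a false late finding is more likely than not. With the largest assumed effect, an SD of differences of 10 would give 64%, but nothing in the protocol supports an SD that small. The other is that the main drug effects are compromised. Readings to 8 h, including the 1.5-3 h peak, are untouched, and hypotheses 2a-2c predict increases, so this bias works against them and cannot create a false positive for them.

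**Conclusion.** The schedule and the planned analysis do not fit together and should be corrected; this is a should-fix point. As written, session 1's 29 h and 30 h values are recorded 5 h and 6 h after the next dose, and the late contrast is biased by -E/2. That is -1.4 to -10.5 VAS points if E is 10-75% of the planning effect. The chance of a significant spurious dip is then 4-31% at an SD of differences of 19, or 4-19% at 27, against 2.5%. The AVI and IAS-R condition effect is diluted, by an amount that depends on decay rates the protocol does not give. Under the Day 3-only reading the contrast is not biased in this way but cannot be formed within volunteer. The timing arithmetic and the factor one-half are firm. The point sizes rest on the assumed E, on carrying an MDMA planning figure over to MDA, and on no true effect remaining at 29-30 h.

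**What to change.** 1. State in Timing of Measures which session's 29 h and 30 h readings are collected.
2. Exclude every session 1 reading taken after the second dose (29 h, 30 h) from the condition-by-time analysis, and end that analysis, for both conditions, at a reading taken before the next dose. This is 7.5 h for AVI and IAS-R. For the cardiovascular, temperature and VAS measures it is 8 h, or 24 h if that reading is confirmed as taken before dose 2. If 24 h is kept, note that session 1's 24 h value is also session 2's predose value.
3. Report the 29-30 h readings after session 2 descriptively, by hours since MDA: 29-30 h in placebo-first volunteers, and 29 + 24 = 53 h to 30 + 24 = 54 h in MDA-first volunteers. Do not test them as drug against placebo.

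The cost is wording in the schedule and the analysis section, with no change to sample size. The downside is that the late readings become a descriptive comparison of 6 with 6 volunteers.

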·	Genotyping for COMT, HTTPLR, 5HT2A, and CYP2D6 

Urine testing will include:
·	Urine toxicology screen (opiates, amphetamine, cocaine, benzodiazepines, MDMA) 
·	Urine pregnancy test for female subjects

Determining CYP2D6 status:  CYP2D6 activity is genetically determined and up to 10% of the Caucasian population has deficient CYP2D6 activity [51].  Either genotyping or phenotyping participants can assess CYP2D6 activity.  Biological samples from subjects will be collected once they are admitted to the GCRC and will be tested for CYP2D6.  
A physician, nurse, or nurse practitioner will conduct a physical examination. 
If necessary, such as in cases where screening results are inconclusive and further tests are needed, additional screening visit(s) may be added.
Experimental sessions:
Experimental sessions at the CCRC at San Francisco General Hospital (SFGH).  Two experimental sessions occur over 2 consecutive days.  Prior to admission and immediately preceding experimental sessions 1 and 2, subjects will be administered a urine toxicology screen and—if female—a pregnancy test.  Timed measurements are made before and after drug administration as described below.  Subjects receive one of two dosing conditions (listed below) per session.  
Subjects are monitored closely before and after, until drug effects resolve or post 8 hours (whichever is later).  
Experimental Drug Doses and Conditions: 
Experimental Dosing Conditions are:
1.	MDA placebo
2.	MDA 98 mg/70 kg body weight
      
Dosing Description and Procedures: In accordance with hospital and other regulations, appropriately licensed personnel will be responsible for administering the study drug.  
Experimental dosing occurs with a 2-hour fast before and a 1.5-hour fast after.  Lactose in a gelatin capsule is used for the MDA placebo.  Placebos are identical in appearance to active drugs.  

Rationale for Experimental Dosing Conditions:  Based on clinical studies, the single MDA dose being given in the present study should produce at most moderate intoxication and stimulant effects that should resolve within 8 hours.  Similar MDA doses have been used in other studies.  The dose is slightly lower than used in our MDMA studies to account for the lower molecular weight of MDA vs. MDMA and facilitate comparisons.

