Repeated measures ANOVA will be used, employing similar strategies as in our other experiments.  Measures for hypotheses are continuous and are analyzed by ANOVA with time as the repeated measure and dose as a between subject factor. After a significant F test, post hoc pairwise comparisons will be performed using Fishers Least Significant Difference (LSD) test.  Effects will be considered statistically significant at P≤0.05.  Data from this and our other MDA studies will be pooled and a population PK/PD models will be fitted to the data using the program WinNonLin (36-39).  A compartmental model will be fitted to MDA, HMA and other metabolite concentration versus time data.  Population pharmacodynamic models will be fitted to the response versus time data, conditioning on the individualized Bayes estimates of the MDA/HMA parameters.

Sample Size: The aims of this experiment are to investigate the pharmacokinetics and pharmacodynamics of MDA. For pharmacokinetics, the data analysis primarily requires a descriptive approach rather than null hypothesis testing. We therefore powered the study based on pharmacodynamic measures, specifically self-report measures (because these tend to show more variation and smaller effects sizes than cardiovascular or neuroendocrine measures after MDA and other compounds similar to MDMA). Feelings of insight are a typical effect of hallucinogens and MDMA-like drugs. After 1.5 mg/kg MDMA, visual analog ratings for this item increased by 28±19 points compared to placebo. This was one of the smaller changes in visual analog items detected after MDMA. To detect a similar change after MDA, a sample size of 11 is required, with a power of 0.80 and assuming a two-sided alpha of 0.05. We will increase this N to 12 to allow balancing of dose order. This sample size should leave us adequately powered to detect changes in other measures. Measures are analyzed using repeated measures ANOVA with condition and time as factors. Sample size is too small to allow analysis of gender effects, so we will not balance gender but will conduct exploratory analyses if there appears to be a gender effect.

	(4d) Subject Selection:  

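### Section 4c declares dose a between-subject factor although the order-balanced two-session design gives each volunteer both MDA and placebo, and a later sentence in 4c leaves the conflict open

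*Protocol*

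**What the plan says.** **Design.** Section 4a: "The study uses a double-blind, placebo-controlled, Latin-square design". Section 4b, under Experimental sessions: "Two experimental sessions occur over 2 consecutive days", and "Subjects receive one of two dosing conditions (listed below) per session". The two conditions are placebo and a single MDA dose. The Sample Size paragraph of 4c explains the step from 11 to 12 volunteers: "We will increase this N to 12 to allow balancing of dose order".

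**Analysis.** The first paragraph of 4c, on the measures for the hypotheses, says they are "analyzed by ANOVA with time as the repeated measure and dose as a between subject factor". The Sample Size paragraph then says: "Measures are analyzed using repeated measures ANOVA with condition and time as factors".

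**Planning effect.** After MDMA, "visual analog ratings for this item increased by 28±19 points compared to placebo". The sample size of 11 is stated "with a power of 0.80 and assuming a two-sided alpha of 0.05".

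**The concern.** No sentence says outright that every volunteer receives both conditions. But dose order can be balanced only if each volunteer has an order, and two conditions over two sessions in a Latin square make a 2×2 crossover. A volunteer cannot sit in both levels of a between-subject factor, so the stated test can be run only by treating one person's two sessions as two people.

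The second analysis sentence does not settle this. It fits a crossover, but it does not call condition within-subject and does not withdraw the first sentence. An analyst could follow either.

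At stake is the error term. A between-subject test of dose compares MDA with placebo against variation between people on 22 df. A crossover analysis uses variation in the within-person difference on 11 df (10 with a session term). If volunteers differ stably from one another, the first test carries that variation into the error and loses precision that the design was built to provide.

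**Working it through.** **Inputs.** From 4c: N = 12; effect 28 points; spread 19; two-sided alpha 0.05.

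Assumptions not in the protocol:
- 19 is the SD of the within-person MDA minus placebo difference (the text does not say what the 19 is).
- The SD is equal under both conditions.
- The correlation ρ between a person's two sessions is 0.3, 0.5 or 0.7.
- The illustrative smaller effect is 14 points, half of 28.

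Time is reduced to one value per session, so the table below describes the dose comparison and not the whole time-by-dose ANOVA.

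**The plan's own figure.** A paired t-test with SD of the difference 19 has standardised effect 28/19 = 1.47. It needs n = 6 for 80% power (power 0.82 at 6, 0.99 at 11). The stated 11 therefore does not reproduce on this reading. It is larger than a paired test needs, and the present point does not depend on it.

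**Standard errors.**
- Paired: 19/√12 = 5.48. With t(11) = 2.201, the half-width at the assumed SD is 12.1.
- Between-subject: per-session SD = 19/√(2(1−ρ)), which is 16.1 / 19.0 / 24.5. SE = SD × √(2/12) = 6.56 / 7.76 / 10.01. With t(22) = 2.074, the half-widths are 13.6 / 16.1 / 20.8.
- The ratio of the two SEs is 1/√(1−ρ) = 1.20 / 1.41 / 1.83.

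Mean half-widths in simulation are slightly smaller (below), because a sample SD averages a little under the true SD.

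**Simulation.** 200,000 replicates of 12 pairs; paired t on 11 df against pooled two-sample t on 22 df.

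| | Paired | Between, ρ = 0.3 | ρ = 0.5 | ρ = 0.7 |
|---|---|---|---|---|
| True size of nominal 5% test | 5% | 2.2% | 0.9% | 0.2% |
| Mean 95% CI half-width (points) | 11.8 | 13.4 | 15.9 | 20.4 |
| Power at 28 points | 99.6% | 99% | 98% | 87% |
| Power at 14 points | 64% | 54% | 38% | 17% |

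At ρ = 0 the between-subject test keeps its size (about 5%). At ρ = 0.8 its power at 28 points is about 66%.

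**Which tests are affected.** In the stated ANOVA, a volunteer's stable level enters the error of the dose main effect. The dose-by-time interaction is tested against within-session variation, from which that level is already removed. With stable volunteer differences only, two separate simulations of the mis-specified interaction test gave sizes between 4.8% and 5.5%. When volunteers also shared time profiles across sessions, the size fell to 1.7% in one variant and 0.15% in another.

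Under Timing of Measures in 4b, the cardiovascular measures, AVI, IAS-R, hormones and BFNE have a predose reading, so a drug effect on them can show as dose-by-time. The SDEQ, APZ-OAV, emotional face task and dot probe task have none. With one reading per session, the stated ANOVA reduces to an unpaired two-sample test.

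**The case against.** The best defence is that this is a drafting slip. Section 4c opens by announcing repeated measures ANOVA, the later sentence lists condition beside time, and both fit a crossover. That is fair as far as it goes: the text does not establish that the data will be analysed unpaired. But the sentence addressed to the hypothesis measures says the opposite, and nothing in the protocol corrects it.

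A reader might also infer more than the documents support:
- **That every P value under hypothesis 2 is wrong.** Most of those measures have predose readings, and the dose-by-time test keeps its size unless time profiles are shared across sessions.
- **That false positives are inflated.** With positive correlation the true size is below 5%. The risk is missed effects and over-wide intervals.
- **That the crossover gains nothing.** The point estimate is the same under either analysis, balanced order still protects it from a session effect, and 12 people still supply 24 sessions.
- **That the trial becomes underpowered at its planning effect.** At 28 points, which 4c describes as among the smaller visual analog changes seen with MDMA, power stays above 80% up to a correlation of about 0.7. The 14-point case is illustrative and appears nowhere in the protocol.

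**Conclusion.** The stated analysis is wrong for this design, and 4c is inconsistent with itself. The harm is certain in kind for the dose main effect and for measures without a predose reading, whenever a person's two sessions correlate. For dose-by-time tests it is conditional on shared time profiles.

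The direction is conservative. Over correlations of 0.3 to 0.7 the interval is about 14% to 73% wider than the paired one (13.4/11.8 = 1.14; 20.4/11.8 = 1.73). The loss of power is small to moderate at 28 points and large at half that effect. These sizes rest on 19 being the SD of the within-person difference, on equal variances, on one value per session, and on correlations that the protocol does not give. The contradiction itself needs none of these assumptions.

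**What to change.** In 4c, delete the phrase that makes dose a between-subject factor. State that condition (MDA, placebo) and time are both within-subject factors, with volunteer as the blocking or random factor, and word the sentence in the Sample Size paragraph to match. For measures with one reading per session, state that the analysis uses the within-volunteer MDA minus placebo difference.

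The cost is one sentence, plus a matching edit in the same section. No new data, volunteers or procedures are needed.
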